## Abstract

****Background**:**

Use of inappropriate drugs is common among institutionalized older people. Rigorous trials investigating the effect of the education of staff in institutionalized settings on the harm related to older people’s drug treatment are still scarce. The aim of this trial is to investigate whether training professionals in assisted living facilities reduces the use of inappropriate drugs among residents and has an effect on residents’ quality of life and use of health services.

****Methods and design**:**

During years 2011 and 2012, a sample of residents in assisted living facilities in Helsinki (approximately 212) will be recruited, having offered to participate in a trial aiming to reduce their harmful drugs. Their wards will be randomized into two arms: one, those in which staff will be trained in two half-day sessions, including case studies to identify inappropriate, anticholinergic and psychotropic drugs among their residents, and two, a control group with usual care procedures and delayed training. The intervention wards will have an appointed nurse who will be responsible for taking care of the medication of the residents on her ward, and taking any problems to the consulting doctor, who will be responsible for the overall care of the patient. The trial will last for twelve months, the assessment time points will be zero, six and twelve months.

The primary outcomes will be the proportion of persons using inappropriate, anticholinergic, or more than two psychotropic drugs, and the change in the mean number of inappropriate, anticholinergic and psychotropic drugs among residents. Secondary endpoints will be, for example, the change in the mean number of drugs, the proportion of residents having significant drug-drug interactions, residents' health-related quality of life (HRQOL) according to the 15D instrument, cognition according to verbal fluency and clock-drawing tests and the use and cost of health services, especially hospitalizations.

****Discussion**:**

To our knowledge, this is the first large-scale randomized trial exploring whether relatively light intervention, that is, staff training, will have an effect on reducing harmful drugs and improving QOL among institutionalized older people.

****Trial registration**:**

ACTRN12611001078943

## **Background**

Polypharmacy and use of inappropriate drugs is very common among frail institutionalized residents
[1-3]. Older people living in nursing homes and institutions are administered an average eight to ten medications
[2,4]. Polypharmacy is a challenge for clinicians, because it is associated with a risk of drug-drug interactions and adverse effects
[5]. In institutional settings, polypharmacy has been defined as using more than eight drugs
[6], or ten or more drugs
[7].

Inappropriate medications for older people have been defined in several different ways
[8-11]. The criteria may be explicit, that is, drug- or disease-oriented, implemented to all patients in a similar way, and thus, simple to use
[12]. The criteria may be also implicit, that is, based on clinical judgment; they may include more complicated domains such as effectiveness, drug-drug interactions, lowest cost or duplications. These kinds of criteria are more comprehensive, but also more complicated to use
[12]. The most widely used international explicit criteria have been developed by Beers’ expert panel
[8,9]. Of Finnish elderly residents in institutional care, 36% were on the Beers’ list of inappropriate drugs
[1,13]. This proportion is similar or lower than those found in respective American or Australian studies
[14,15]. Use of inappropriate medications may not increase mortality, but it may result in unnecessary hospitalizations
[16].

The Omnibus Budget Reconciliation Act of 1987 in the USA succeeded in decreasing the use of harmful psychiatric medications among older people
[17]. There have been warnings concerning the use of antipsychotics in patients with dementia, with an increased risk of stroke and mortality
[18,19]. The use of psychotropic drugs is associated with risk of falls
[20]. There is extensive use of psychotropic drugs in Finnish nursing homes, 80% being administered at least one psychotropic drug
[4].

There is also increasing evidence of the adverse effects of drugs with anticholinergic properties. In addition to the traditional side effects such as dryness of mouth, constipation and worsening glaucoma, they have been shown to be associated with cognitive decline
[21,22], and they may increase the risk of hospital admissions
[23]. They may be particularly harmful for older people with cognitive decline and dementia, such as for those in institutional care. In recent studies, particular attention has been paid to the use of anticholinergic drugs and defining them
[22,24].

The criteria of the Swedish National Board of Health and Welfare (Socialstyrelsen) for inappropriate drugs for older people include also the long-term use of nonsteroidal anti-inflammatory drugs (NSAID) and tramadol
[7]. There is also increasing evidence that long-term use of proton pump inhibitors (PPI) among frail elderly institutionalized residents is associated with infections, hip fractures and even higher mortality
[25].

Drug-drug interactions are of concern and they are associated with adverse events
[26]. Swedish Finnish INteraction X-referencing (SFINX) is a commercial medical interaction database that includes information on >6200 drug-drug interactions and it is updated quarterly by specialists in clinical pharmacology
[27]. The potential drug-drug interactions in the SFINX database are classified according to their clinical significance and level of documentation. Clinical significance is classified from A to D, where A means the interaction is clinically insignificant and D means the interaction is clinically significant and the combination should be avoided
[26].

At least 20 randomized controlled studies have been performed aiming to reduce the use of potentially inappropriate drugs among older people living in nursing homes. However, most studies have been of low quality, and thus, have risk of bias
[28]. According to a recent systematic review, interventions using educational outreach, on-site education and pharmacist medication reviews may reduce inappropriate drug use
[28]. Successful educational interventions have been performed to decrease the use of psychotropic medications for institutionalized elderly patients
[29-33] and to improve the quality of drug prescribing
[34,35]. However, only a few studies have explored the intervention effects on older people’s well-being or their use of health services.

The aim of this study is to determine whether training nurses in assisted living facilities in Helsinki would reduce the use of inappropriate medications, anticholinergic and psychotropic drugs among the residents in these houses. In addition, we will examine the effect of intervention on quality of life (QOL), cognition, and use and costs of health services of the participating older people.

## **Methods**

### **General design**

The study is a randomized controlled trial in which wards in assisted living facilities in Helsinki are randomly allocated to two arms. The staff in intervention wards will receive two half-day training sessions concerning appropriate use of drugs among frail older people. Approximately 212 patients will be included: 100 subjects in the intervention group and 100 in the control group. The number of patients per group may vary, because the wards randomized may vary in size. The study has been approved by the ethics committee of Helsinki University Central Hospital. Informed consent has been obtained from each patient and/or their closest proxy before any study procedure is performed according to good clinical practice.

### **Participants**

Older residents residing in assisted living facilities in Helsinki will be recruited one by one by approaching them and their closest proxy.

Inclusion and exclusion criteria for residents in assisted living facilities:

– 65 years or older, living permanently in assisted living facilities in Helsinki

– a native speaker of the Finnish language

– uses at least one drug

– no terminal illness (estimated prognosis >6 months), and

– voluntary participation, written informed consent to participate in the study given by participant or her/his closest proxy.

Those residents fulfilling the inclusion criteria are invited for the first study nurse visit. In case of the participants’ cognitive decline (Mini Mental State Examination (MMSE) <20)
[36] or poor judgment capability, the proxy is invited to give consent in addition to the participant.

### **Study procedures**

The baseline study visit lasts about one hour and includes an interview to ascertain residents’ demographic data, diagnoses, and medications used. The diagnoses and medications are confirmed from medical records.

The participant will be assessed using the clinical dementia rating scale (CDR)
[37], Mini Mental State Examination (MMSE)
[36], verbal fluency
[38,39], the clock-drawing test
[40], and Mini Nutritional Assessment (MNA)
[41]. Patients’ psychological well-being will be assessed using the psychological well-being (PWB) scale
[42] and health-related quality of life (HRQOL) will be assessed by 15D measure
[43]. Participants will be assessed by two study nurses three times during the year: at baseline, and at six and twelve months. The flow chart of the study is presented in Figure
1, and study assessment procedures are described in Table
1. Hospitalizations, use of other health and social services and death dates will be retrieved from the central registers for one year from baseline measurements.

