**Figure 1 F1:**
[figure not shown]
Flow chart.

**Table 1 T1:** Study assessment procedures and timetable

**Assessment**	**Comparability of wards; interview**	**Baseline assessment**	**Six-month assessment**	**Twelve-month assessment**
Inclusion criteria, informed consent	X			
Demographics, diagnoses		X		
CDR		X		
MMSE		X	X	X
Verbal fluency, clock-drawing test		X	X	X
MNA		X		
Drug use		X	X	X
15D QOL measure		X	X	X
PWB scale		X	X	X
RAI assessment	X	X	X	X
Falls			X	X
Hospitalization, use of health and social services, mortality				X
X				

CDR, clinical dementia rating scale (Hughes et al. 1982); MMSE, Mini Mental State Examination (Folstein et al. 1972); MNA, Mini Nutritional Assessment (Guigoz et al. 2002); 15D, health-related quality of life scale (Sintonen et al. 1990); PWB, psychological well-being scale (Routasalo et al. 2009); RAI, Resident Assessment Instrument (Morris et al. 2000).

Drug use will be assessed as the point prevalence on the day of assessment. Residents will be classified as regular drug users if their medical charts indicate a regular sequence of administration on a daily basis. Additional analyses will be performed including both regularly used drugs as well as drugs used on a *pro re nata* (*prn*, or as needed) basis. The drugs administered to residents will be classified according to the anatomical therapeutic chemical (ATC) classification system recommended by the World Health Organization (WHO)
[44]. The drugs that will be considered as inappropriate, having anticholinergic properties or being psychotropic drugs are presented in Additional file
1: Table S1. The total number of these drugs each resident is using one, on a regular daily basis and two, both regularly or *prn* will be counted.

We randomized wards instead of individual participants in order to avoid contamination. The wards selected for this study were all using the Minimum Data Set (MDS)/Resident Assessment Instrument (RAI) version 2.0 for home care

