### **Outcome measurements**

The research nurses perform their assessments at zero, six and twelve months.

Primary outcome measures are:

· the proportion of persons using inappropriate, anticholinergic or more than two psychotropic drugs (these drugs are presented in Additional file
1: Table S1), and

· the change in the mean number of inappropriate, anticholinergic and psychotropic drugs.

Secondary outcome measures are:

· change in the mean WHO-defined daily dose
[44] of inappropriate, anticholinergic or psychotropic drugs

· the proportion of persons with significant drug-drug interactions according to SFINX
[27]

· the number of drug-related problems
[46]

· change in the mean number of drugs

· change in the proportion of participants having nine or more drugs

· use of health care services and their costs during a 12-month follow-up

· the number of hospitalizations/follow-up time

· the 15D HRQOL measure
[43]

· cognition according to verbal fluency and clock-drawing test
[38-40], and CDR sum of boxes
[37]

· change in neuropsychiatric symptoms or symptoms of delirium according to the RAI instrument
[45], and

· the number of fallers according to the RAI instrument
[45].

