### **Statistical analyses**

Required sample size calculation is based upon the change in the proportion of users of inappropriate, anticholinergic or psychotropic drugs. Sample size was calculated as follows: if in the control group 36% use inappropriate drugs, the minimum group difference with the assessment is 20%, type I error 5%, power 80%, which results in 106/group. Because we recruit participants from wards and aim to include as many as possible from those wards, the final sample size may differ slightly from this figure.

In these baseline findings, for the continuous variables, descriptive values will be expressed by means with standard deviations (SD) and medians with range. For the variables with a normal (Gaussian) distribution, statistical comparisons between the groups will be made by using a *t* test. If the variables have a non-normal distribution or ordinal level, statistical comparison between groups will be performed with the Mann Whitney *U* test. Measures with a discrete distribution will be expressed as percentages (%) and analyzed by *X*^2^ or Fischer’s exact test when appropriate.

The results will be analyzed according to intention to treat. For imputation method, ‘the last observation carried forward’ (LOCF) and ‘worst-rank score’ principle will be used. For the most important outcome parameters, estimation of confidence interval (95%) will be used in addition to testing. Since the distributions of health care costs are highly skewed, the differences between means and confidence intervals are estimated using the bootstrap method (bias corrected and accelerated bootstrapping).

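### Register data are collected only from baseline onward, so chance differences between arms in prior hospital use cannot be checked or adjusted for, and some precision is lost (minor, cheap to improve)

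*Protocol article*

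**What the plan says.** Under Study procedures, the register data on hospitalizations, other health and social services and deaths "will be retrieved from the central registers for one year from baseline measurements". The window therefore runs forward only.

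The outcomes match that window. Under Outcome measurements, two secondary outcomes are "use of health care services and their costs during a 12-month follow-up" and "the number of hospitalizations/follow-up time". Neither is a change from an earlier value. The abstract puts weight on "the use and cost of health services, especially hospitalizations".

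For costs, Statistical analyses begins "Since the distributions of health care costs are highly skewed" and then says that "the differences between means and confidence intervals are estimated using the bootstrap method". No pre-baseline service use appears anywhere in the article.

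On allocation, Study procedures says "We randomized wards instead of individual participants in order to avoid contamination". It adds that wards are paired on their case-mix profile from the resident assessment instrument (RAI) before randomization.

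In Table 1, drug use, 15D, verbal fluency, clock drawing and RAI are marked at baseline. The row "Hospitalization, use of health and social services, mortality" shows a mark at twelve months, but a loose X follows on the next line and its column cannot be told. The point therefore rests on the sentence in Study procedures and not on the table.

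**The concern.** Past use of hospitals and services may well predict future use. Three features of this trial make such a value useful:

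- Whole wards are allocated, so chance differences between arms tend to be larger than under individual allocation.
- The pairing uses case-mix. Prior hospital use is not named as a pairing factor.
- Costs are skewed, so a few heavy users can move an arm's mean.

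If one arm happens to contain wards or residents with more hospital use before the trial, the plan provides nothing that would show it and no prior value to adjust for. At stake are the precision and credibility of two secondary outcomes. The Discussion presents data on hospitalizations as something many previous trials lacked.

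**Working it through.** **Inputs from the document.** The register window is one year forward from baseline (Study procedures). Both service outcomes are defined over follow-up only (Outcome measurements). The sample size is 106 per group (Statistical analyses). That figure was derived for the proportion of users of inappropriate drugs. It serves here only as an arm size. The article states no power or precision for hospitalizations or costs, so there is no figure of its own to reproduce.

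**Assumed inputs.** The correlation r between prior-year and follow-up use is taken as 0.1 to 0.5. For step 4, an intraclass correlation (ICC) of 0.05 and 10 to 20 residents per ward are assumed. The document gives none of these.

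**1. Variance after adjustment.** Residual variance is multiplied by 1 − r². The equivalent gain in sample size is 1/(1 − r²) − 1.

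| r | 1 − r² | Variance removed | Equivalent extra residents |
|---|---|---|---|
| 0.1 | 0.99 | 1% | 1% |
| 0.2 | 0.96 | 4% | 4% |
| 0.3 | 0.91 | 9% | 10% |
| 0.5 | 0.75 | 25% | 33% |

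**2. Detectable difference.** At two-sided 5% and 80% power, ignoring clustering, the unadjusted value is (1.960 + 0.842) × √(2/106) = 0.385 SD. Multiplying by √(1 − r²) gives:

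- r = 0.1: 0.385 × 0.995 = 0.383 SD
- r = 0.3: 0.385 × 0.954 = 0.367 SD
- r = 0.5: 0.385 × 0.866 = 0.333 SD

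**3. Effect of a chance imbalance.** If the arms differ by d SD in prior use, the unadjusted estimate shifts by r × d. For d = 0.2:

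- r = 0.1: 0.1 × 0.2 = 0.02 SD
- r = 0.3: 0.3 × 0.2 = 0.06 SD
- r = 0.5: 0.5 × 0.2 = 0.10 SD

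**4. How often such an imbalance might occur.** The design effect is 1 + (m − 1) × 0.05, which is 1.45 for m = 10 and 1.95 for m = 20. The SD of the difference between arms is √(2/106 × 1.45) = 0.17 to √(2/106 × 1.95) = 0.19, in units of the resident-level SD. A gap of at least 0.2 SD in either direction then has a probability of about 23% to 30%. This ignores any reduction from pairing, so it leans high if the pairing factors are related to hospital use.

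**Limits of the arithmetic.** Steps 1 to 3 use an individual-level linear model. Costs are skewed, hospitalizations are a rate over follow-up time, and wards are randomized. With clustering, the gain depends separately on the within-ward and between-ward correlations. The percentages are a guide to order of magnitude.

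**The case against.** The strongest reply is that nothing here is wrong. The register window and the outcome definitions agree, and follow-up rates and costs can be compared validly between randomized arms without a prior value. Choice of covariates is usually left to an analysis plan. That stands as far as validity goes, and the absence of a named covariate is not the point. The forward-only window, however, is stated outright, and an analysis plan cannot adjust for data that are not collected.

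A reader might infer that a starting difference in hospital use would bias the trial, or that there is no protection against ward imbalance. The document does not support either reading. Wards are randomized within case-mix pairs, so the comparison is unbiased in expectation. Diagnoses, CDR, MMSE, MNA and RAI are recorded at baseline and can serve as covariates. Protection is reduced and not absent.

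A reader might also take a gain of 9% to 25% as established. It is not. It holds only for an assumed r of 0.3 to 0.5, and it would normally shrink once the other baseline covariates are in the model. Prior use could also be a weaker predictor than hoped. Eligibility requires permanent residence but no minimum stay, so a recent arrival's earlier year would partly reflect life before the ward. The Discussion also expects competing complications and deaths.

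Finally, the document does not describe how far back the registers reach or what permission covers. If earlier records exist they might still be requested later, so the loss need not be final. These objections lower the severity. They do not remove the point.

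**Conclusion.** The point holds as a low-cost improvement of minor severity. The protocol collects service use only after baseline, so two of its eleven secondary outcomes lack the earlier value that drug use, 15D and the verbal fluency and clock-drawing tests have. The consequence is some lost precision, and a chance difference in prior use that cannot be directly checked or adjusted for.

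The benefit forgone runs from negligible at r = 0.1 to material at r = 0.5, and which applies cannot be settled from the document. The estimate rests on the assumed r and on an individual-level approximation. The frequency of imbalance rests in addition on an assumed ICC and ward size. The primary drug-use outcomes are unaffected.

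**What to change.** - In Study procedures, extend the same register request to cover the 12 months before baseline as well as the 12 months after.
- Report prior-year hospitalizations and service use by arm with the baseline characteristics.
- Prespecify the resident's prior-year value as a covariate in the hospitalization-rate and cost comparisons. Use models suited to count and skewed data that respect the randomization by ward.

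The cost is a wider date range and one covariate, with no added visits or burden for residents. The conditions are that consent and register permission cover the earlier year and that the registers hold those records. Trial status reports recruitment as incomplete at submission, so these conditions could be checked early. For residents already enrolled, the scope of the consent they gave needs checking.

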**Figure 1 F1:**
[figure not shown]
Flow chart.

**Table 1 T1:** Study assessment procedures and timetable

**Assessment**	**Comparability of wards; interview**	**Baseline assessment**	**Six-month assessment**	**Twelve-month assessment**
Inclusion criteria, informed consent	X			
Demographics, diagnoses		X		
CDR		X		
MMSE		X	X	X
Verbal fluency, clock-drawing test		X	X	X
MNA		X		
Drug use		X	X	X
15D QOL measure		X	X	X
PWB scale		X	X	X
RAI assessment	X	X	X	X
Falls			X	X
Hospitalization, use of health and social services, mortality				X
X				

CDR, clinical dementia rating scale (Hughes et al. 1982); MMSE, Mini Mental State Examination (Folstein et al. 1972); MNA, Mini Nutritional Assessment (Guigoz et al. 2002); 15D, health-related quality of life scale (Sintonen et al. 1990); PWB, psychological well-being scale (Routasalo et al. 2009); RAI, Resident Assessment Instrument (Morris et al. 2000).

Drug use will be assessed as the point prevalence on the day of assessment. Residents will be classified as regular drug users if their medical charts indicate a regular sequence of administration on a daily basis. Additional analyses will be performed including both regularly used drugs as well as drugs used on a *pro re nata* (*prn*, or as needed) basis. The drugs administered to residents will be classified according to the anatomical therapeutic chemical (ATC) classification system recommended by the World Health Organization (WHO)
[44]. The drugs that will be considered as inappropriate, having anticholinergic properties or being psychotropic drugs are presented in Additional file
1: Table S1. The total number of these drugs each resident is using one, on a regular daily basis and two, both regularly or *prn* will be counted.

We randomized wards instead of individual participants in order to avoid contamination. The wards selected for this study were all using the Minimum Data Set (MDS)/Resident Assessment Instrument (RAI) version 2.0 for home care
[45]. MDS is used for assessing the residents’ needs and for individual care planning purposes. Each nurse has been educated to use MDS, and the assessment is routinely performed twice annually or whenever there is a substantial change in the resident’s status. In addition to the internationally well-validated scales and items, MDS provides a patient’s ward profile, often called ‘the case-mix’ (for example, ‘psychogeriatric’, ‘physically disabled’ or ‘cognitively impaired’), and gives the mean level of residents’ need for assistance. After identifying the case-mix in each of the wards, the wards will be divided into dyads having approximately the same characteristics. These dyads will be further randomized, by means of computer-generated random numbers, into two arms: those to receive staff training or to receive education after the trial. In addition, individual RAI items (for example, the proportion of fallers) and some of the well-validated RAI scale items (for example, neuropsychiatric symptoms, symptoms of delirium) will be used in measuring the effects of intervention.

